# Lifestyle intervention in BRCA1/2 mutation carriers: study protocol for a prospective, randomized, controlled clinical feasibility trial (LIBRE-1 study)

**DOI:** 10.1186/s40814-016-0114-7

**Published:** 2016-12-19

**Keywords:** BRCA1, BRCA2, Hereditary breast cancer, Hereditary ovarian cancer, Lifestyle intervention

## Abstract

**Background:**

Women with highly penetrant BRCA mutations have a 55–60% lifetime risk for breast cancer and a 16–59% lifetime risk for ovarian cancer. However, penetrance differs interindividually, indicating that environmental and behavioral factors may modify this risk. These include lifestyle factors such as physical activity status, dietary habits, and body weight. The modification of penetrance by changing lifestyle factors has not thus far been investigated in a randomized trial in BRCA mutation carriers.

**Methods:**

Therefore, we intend to enroll 60 BRCA1/2 mutation carriers in a pilot feasibility study (Lifestyle Intervention Study in Women with Hereditary Breast and Ovarian Cancer (LIBRE) pilot). This multi-center, prospective, controlled trial aims to randomize (1:1) participants into a (1) multi-factorial lifestyle intervention group (IG) versus (2) the control group with usual care (CG). The primary endpoint is feasibility and acceptance of a structured interdisciplinary lifestyle intervention program over 12 months (at least 70% of the patients to complete the 1-year intervention). Furthermore, the effects on physical fitness, BMI, quality of life, and stress coping capacity will be investigated.

During the first 3 months, women in the IG will receive structured, individualized and mainly supervised endurance training of ≥18 MET*h/week (MET = metabolic equivalent task) and personal nutritional counseling based on the Mediterranean diet. During the subsequent 9 months, the IG will receive monthly group training sessions and regular telephone contacts for motivation, whereas the CG will only receive usual care (one general counseling on healthy nutrition and benefits of regular physical activity on health status). At randomization and subsequent time points (3, 6, 12 months), cardiopulmonary fitness will be assessed by spiroergometry and nutritional and psychological status by validated questionnaires.

**Discussion:**

This pilot study will investigate the optimal strategy to improve physical fitness, nutritional habits, and psychological factors in women at high risk for developing breast or ovarian cancer. The results of this pilot feasibility study will be the basis for a larger prospective randomized trial including clinical events (LIBRE).

**Trial registration:**

ClinicalTrials.gov, NCT02087592

## Background

Tumor suppressor genes, such as breast cancer (BRCA)1 and 2, are important regulators for suppressing tumor development. Women with highly penetrant BRCA mutations have a lifetime risk of 55–60% for breast cancer and 16–59% for ovarian cancer [1, 2]. Penetrance rates vary because of endogenous factors, such as gene polymorphisms, as well as exogenous factors, such as the number of pregnancies, year of birth, and physical activity during youth [3, 4]. The risk for breast cancer is lower if genotype carriers were born before 1940, gave birth, or were physically active during their youth [5, 6].

Prospective studies have revealed that regular physical activity can significantly reduce breast cancer incidence in post- and premenopausal women, the risk being reduced on average by 25% [7]. Furthermore, the risks of recurrence and mortality in women with breast cancer are reduced by 50% if they engage in regular physical activity [8]. Further advantages of physical activity include a gain in quality of life, increased fitness, and improved tolerance of chemotherapy [9].

Nutrition also influences the risk of breast cancer. Obesity and weight gain increase the risk of breast cancer in both pre- and postmenopausal subjects [10, 11]. A weight gain of more than 20 kg after the age of 18 doubles the risk of breast cancer. Furthermore, women with a body mass index (BMI) of >30 kg/m^2^ have a greater risk of developing distant metastases and early mortality [12]. In a prospective study with sporadic breast cancer on patients under adjuvant standard therapy, a calorie and fat-reduced nutrition program led to a significant reduction in recurrence rates [13].

Further risk factors for breast cancer include depression, a pessimistic outlook on life, and problems in coping with stress [14, 15]. Numerous studies have overwhelmingly documented the substantial significance of an optimistic life perspective for different psychological and somatic disorders [16]. A positive association was shown between an optimistic outlook on life and psychological well-being, health, stress reduction, and mortality, as well as improved recovery rates [17–19].

So far, no studies have been performed prospectively assessing lifestyle intervention in women with hereditary breast cancer or women with a deleterious BRCA mutation. Even retrospective data analysis is rare. There is currently only one publication on this subject by Manders et al. in 2011 [20], which reports on an association between increased body weight and an increased risk for breast cancer in BRCA1/2 mutation carriers.

Therefore, we aim to perform a large randomized intervention trial assessing whether a long-term multifactorial lifestyle intervention program, including (1) a structured physical endurance training, (2) nutritional counseling stressing the Mediterranean dietary pattern, and (3) stress coping strategies, will lead to a reduction in breast cancer incidence and mortality in BRCA1 and 2 mutation carriers (Lifestyle Intervention Study in Women with Hereditary Breast and Ovarian Cancer (LIBRE)). Before this large trial can be started, we will execute a feasibility study (LIBRE-pilot), which is outlined here. This smaller trial with 60 patients will evaluate whether women will be compliant and will sufficiently adhere to a demanding intervention program. Based on the results of this first pilot trial, we aim to set up a subsequent larger trial to investigate the efficacy of the intervention on clinical endpoints. The present paper describes the objectives and design of the feasibility trial, hereafter shortly referred to as “LIBRE-1” (Lifestyle Intervention Study in Women with Hereditary Breast and Ovarian Cancer, 1 = pilot).

## Methods

### Trial design

LIBRE-1 will be a multicenter, prospective, two-armed randomized (1:1) controlled clinical trial including *n* = 60 BRCA1 or 2 carriers. The aim of the study is to evaluate adherence to and acceptance of a structured, 1-year exercise program combined with a Mediterranean dietary pattern in BRCA mutation carriers. Additionally, physical fitness, body weight, quality of life, and stress coping capacity will be assessed. The study design is outlined in Fig. 1 and includes four visits (study entry (SE), start of intervention (V0), 3 months after start of intervention (V1), and 12 months after start of intervention (V2)). The schedule of enrollment, interventions, and assessments is shown in Table 1.

**Fig. 1 Fig1:**
[figure not shown]
Design of the trial

**Table 1 Tab1:** Schedule of enrolment, interventions, and assessments

	Enrolment	Start	3 months	6 months	9 months	12 months	24 months	36 months	+12 months
Visit	SE	V0	V1	V1–6	V1–9	V2	V3	V4	Follow-up
Enrolment									
Eligibility screen	X								
Informed consent	X								
Randomisation	X								
Interventions									
Intervention group (I)	X	X	X	X	X	X	X	X	X
Control group (C)	X	X				X	X	X	X
Assessments									
Clinical baseline	C + I								
Clinical follow up						C + I	C + I	C + I	C + I
Spiroergometry	C + I		C + I			C + I			
Accelerometry	C + I		C + I	C + I	C + I	C + I			
Questionnaire “training” (IPAQ-L)		C + I	C + I	C + I	C + I	C + I	C + I	C + I	
Questionnaire “nutrition” (MEDAS, EPIC-FFQ)	C + I		C + I	I	I	C + I	C + I	C + I	
Lab	C + I		C + I			C + I	C + I	C + I	
Clinical examination	C + I		C + I			C + I	C + I	C + I	
Anthropometry	C + I		C + I			C + I	C + I	C + I	
Psychological questionnaires	C + I		C + I			C + I	C + I	C + I	

### Participants

The goal is to recruit a minimum of 60 patients for the feasibility study. Recruitment and study conduct take place at three centers in three different regions in Germany (Munich, Kiel, and Cologne). Patients will be recruited from the German Consortium Hereditary Breast and Ovarian Cancer (GC-HBOC), a national registry for BRCA1 and 2 carriers. BRCA1- or 2-positive participants have been included in this surveillance program before and are contacted on a regular basis regarding clinical events. They have previously received genetic analysis mainly because of an amplified family history for breast cancer. They have received additional counseling before and are aware of their cancer lifetime risks. Table 2 details the study’s inclusion and exclusion criteria. Contacting the carriers for potential inclusion in the LIBRE-1 study will be done by the local study centers which are familiar with the patient history. Patients will either be contacted by telephone or during their regular visits to the hospital. Information regarding the LIBRE-1 trial will be given in person by physicians involved in the GC-HBOC program and previously instructed regarding the LIBRE-1 study. If patients agree to participate in the trial, they will have to sign consent forms and, if eligible, will be enrolled into the trial.

**Table 2 Tab2:** Study population: inclusion and exclusion criteria

Inclusion criteria (all criteria must apply): • Women with a pathogenic BRCA1 or BRCA2 germline mutation • Age between 18 and 69 years • Written informed consent	
Exclusion criteria: • Metastatic tumor disease • Expectancy of life <3 years • Limited cardiovascular and lung diseases (instable CHC, heart failure stage IV, COPD GOLD IV, maximal blood pressure at rest >160/100 mmHg) • Significant orthopedic problems, not allowing exercise • Serious diseases, not allowing a participation in group interventions (e.g., psychiatric or internal ailment) • Karnofsky status scale <60% • Women with VO_2_ max > 150% of general population • Women with an exercise capacity <50 W • Food allergies not allowing consumption of a Mediterranean dietary pattern • Vegans • BMI < 15 kg/m^2^ • Pregnancy • Insufficient knowledge of the German language • Current participation in other lifestyle intervention trials	

### Intervention

#### Intervention group

The intervention program group is designed to last 12 months. The first 3 months includes intensive (regular) contact with physical activity and nutritional education sessions. The learned strategies will then be maintained and monitored in the following 9 months through monthly contacts and meetings. The lifestyle intervention program comprises the following measures:
*Physical activity*: The LIBRE training program is primarily an endurance-oriented training, which will be completed in the course of 1 year. After a mandatory introductory lecture on the theory behind the intervention training, the goal is to increase physical activity to ≥18 MET*h/week (MET = metabolic equivalent task). One MET is equivalent to resting energy expenditure, so multiple METs express exercise intensity that is performed over a certain time, e.g., hours per week. 18 MET*h/week is approximately equivalent to brisk walking (4.5 MET) for 4 h per week. This activity level has been correlated consistently with a reduction of morbidity and mortality in breast cancer patients [8, 21]. This goal should be achieved within the first 12 weeks and maintained throughout the whole study period. Each subject will receive an individual training plan, which will continuously be adapted according to her fitness status. The training plan is divided into two phases: the intensity of the initial phase, weeks 1–6, should be at least 50–60% of the peak oxygen consumption (VO_2_ peak), and the optimization phase, weeks 7–12, 60–75% of the VO_2_ peak. In the first 12 weeks of the intervention program, training will take place twice a week as supervised training and once a week as home-based training (HBT). Afterwards, supervised training units will only be carried out monthly, so that training in months 4–12 will be mainly HBT. Training will continue to take place with an intensity of at least 60–75% of the VO_2_ peak in accordance with the individual training plan.A record of compliance with the training intervention program as well as the achieved MET*h/week will be kept in the training diaries (questionnaire on physical activity, V0–V2). Participants should record their daily activities as well as intentional physical activity including intensity and duration of training. The training intensity levels will then be assessed by spiroergometry and outlined in the diary, which facilitates training control. Monthly supervised training units (as of V1) offer the opportunity to realign training intensity and discuss any problems with adherence to training. In addition, physical activity is to be recorded using questionnaires (International Physical Activity Questionnaire (IPAQ) [22, 23] from V0 to V2), motion sensors (accelerometer from SE to V2), and a physical fitness assessment by cardiopulmonary exercise testing by spiroergometry (VO_2_ peak) [24] at time points SE, V1, and V2.
*Nutrition*: Within the framework of the LIBRE-1 study, the nutrition intervention is based on the principles of a Mediterranean dietary pattern (MD). Furthermore, obese patients (BMI ≥ 35 kg/m^2^) will be instructed to limit their energy (kcal) intake. Nutrition intervention in the IG consists of an intensive phase of 3 months in line with the intensive physical exercise program. During this phase, bi-weekly nutrition education group courses will be held by dietitians. They include a cooking class and guided tour of a supermarket. Afterwards, nutrition courses will be reduced to monthly intervals. The main objective of the nutrition intervention is to provide practical nutritional training, which should enable the subjects to achieve a long-term change in their eating habits, replacing it with the MD. Eating habits will be recorded using validated questionnaires (EPIC-Food Frequency Questionnaire (FFQ) and Mediterranean Diet Adherence Screener (MEDAS)) at the time points SE, V1, and V2. The questionnaires are described below in the “Measurements” section.
*Psychological support*: Explicit psychological support is not planned. Psychological support of the IG will comprise solely of an explanation of the psychological data survey questionnaires given to the study participants. The participants will be informed that the objective of the lifestyle study is, among others, that the lifestyle change including regular physical activity and healthy eating should lead to an improvement in general life quality, stress reduction, and a more optimistic outlook on life. In order to verify this, the participants will receive questionnaires (Screening Scale for Chronic Stress (SSCS), Life of Orientation Test-Revised (LOT-R), European Organisation for Research and Treatment of Cancer (EORTC) Quality of Life Questionnaire Core 30 and Breast Cancer Module 23 (QLQ-C30/-BR23), and Assessment of physical activity and nutrition (BKAE)) at several time points (SE, V0, V1, V2). Advice on the psycho-oncological aspects of the LIBRE study will be given during the introduction lecture at the beginning of the study. The psychological advice given to the study participants will serve to inform the subjects of the significance and improvement of psycho-social lifestyles for the prevention of breast and ovarian cancer, as well as to promote compliance and recognize possible psychological impediments for participation in the study.

#### Control group

The CG will receive a mandatory introduction lecture on the positive effects of physical activity on the incidence and prognosis of breast cancer. Afterwards, all participants will be given a brochure providing the most important facts on this topic. In contrary to the IG, no training and no physical activity diaries will be provided. Changes in physical activity behavior are however to be measured identically to the interventional group by questionnaires (IPAQ from V0 to V2), motion sensors (accelerometer SE–V2), and examinations of physical exercise capacity (VO_2_ peak) at the time points SE, V1, and V2. Additionally, a dietitian-led group lesson on healthy eating will be held for the CG/UC. During this lesson, the subjects will receive general information based on the recommendations of the German Society of Nutrition, which is referred to as “usual care in Germany” in this study. Eating habits will be recorded identically to the intervention group via validated questionnaires (EPIC-FFQ and MEDAS questionnaire) at the defined time points SE, V1, and V2.

Finally, the control group will receive an explanation of the psychological data entry forms, given to the study participants. An explicit psycho-oncological intervention strategy is also not intended in this group. The participants will be informed that changes in daily routine concerning physical activity and dietary habits among other things should result in the improvement of quality of life, a reduction of stress, and a more optimistic approach to future life. In order to verify this, the participants will receive questionnaires (SSCS, LOT-R, EORTC QLQ-C30/-BR23, LIBA, and BKAE) at SE, V0, and V2. The psychological information of the CG/UC corresponds to those of the IG.

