#### International Physical Activity Questionnaire

The IPAQ comprises five areas of activity, which are examined independently of each other [28]. The questionnaire is a simple instrument, which can be used to collect internationally comparable data for health-promoting physical activity over the last 7 days. The IPAQ is to be assessed at all study time points (SE–V2).

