### Study endpoints

The primary endpoint of the study is the number of randomized women who successfully complete the first 3 months of the intervention program and the monitoring/maintenance phase after 1 year. The study is considered feasible if at least 70% of the patients fulfill the criteria (see Table 4 for details).

**Table 4 Tab4:** Criteria for successful completion

Attendance of 70% of the planned lifestyle intervention events (training sessions and nutrition courses) within the first 3 months • Conduct of study visit after 1 year • No withdrawal of informed consent within 1 year • No new occurrence of any of the exclusion criteria during the first 3 months	

Secondary endpoints of the study include the measurements of quality of life (EORTC QLQ-C30-/BR23), stress coping (SSCS), optimism grade (LOT-R), body mass index (BMI), eating habits, nutrient and fat calorie intake (EPIC-FFQ), adherence to a Mediterranean diet (MEDAS), maximal oxygen intake (VO_2_ max), and physical activity (IPAQ). These measurements will be performed after 3, 6, and 12 months of intervention and compared to the baseline measurements at SE.

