### Statistical analysis and randomization

The sample size for the feasibility study is to be at least 60 women. For this study, the sample size was not determined based on statistical assumptions and tests, but on practical grounds that each center should recruit 20 participants. Primary and secondary endpoints will be analyzed descriptively. The primary endpoint will be determined according to the criteria shown in Table 4. Secondary endpoints will be described using absolute or relative frequencies, means with standard deviations, or medians with inter-quartile ranges as appropriate, for each of the study arms at the different time points. Measurements at months 3, 6, and 12 will be compared and tested against the baseline values using either parametric or non-parametric tests as appropriate. Randomization is to take place using envelopes, which will be deposited at the study center before the study begins. The group allocation (randomization) will be done centrally, using randomly permuted blocks of length 2–6. The randomization ratio is to be 1:1. We will use participating center and previous breast cancer as stratification factors. Each center will receive consecutively numbered, opaque envelopes, unique to them, split into two sets (one for previously diseased and one for healthy participants), containing the results. For each new participant, the principal investigator in the center will choose and open the first envelope from the diseased or healthy batch accordingly. As the study is not blinded, the allocation result will be concealed neither from participants nor from the principle investigators.

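### The baseline of the physical-activity endpoint (IPAQ) is defined inconsistently: the endpoint text needs a study-entry value that Table 1 and both group descriptions do not schedule

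*Protocol article*

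**What the plan says.** **Endpoint and its baseline.** Study endpoints lists "maximal oxygen intake (VO_2_ max), and physical activity (IPAQ") among the secondary endpoints. IPAQ is the only activity measure named there; accelerometry is not named. The same section fixes the reference value: "These measurements will be performed after 3, 6, and 12 months of intervention and compared to the baseline measurements at SE". Statistical analysis and randomization then tests months 3, 6 and 12 against baseline.

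**When IPAQ starts.** The article gives two answers.
- At SE: the International Physical Activity Questionnaire paragraph says "The IPAQ is to be assessed at all study time points (SE–V2").
- At V0: Control group has "questionnaires (IPAQ from V0 to V2), motion sensors (accelerometer SE–V2), and examinations of physical exercise capacity". Intervention group has the IPAQ "from V0 to V2), motion sensors (accelerometer from SE to V2"). In Table 1 the row "Questionnaire “training” (IPAQ-L") is empty at SE and is first marked, for both arms, in the Start column (V0).

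**When women learn their arm.** Table 1 puts randomisation in the SE column. Statistical analysis and randomization says "the allocation result will be concealed neither from participants nor from the principle investigators".

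**Recall window.** The questionnaire covers "health-promoting physical activity over the last 7 days".

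**Accelerometry.** Table 1 marks it for both arms at SE and at 3, 6, 9 and 12 months.

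**The concern.** A change-from-baseline endpoint needs a baseline that exists and, in an open trial, one recorded before participants know their group. On the schedule in Table 1, IPAQ meets neither condition: the SE value required by Study endpoints is not collected, and the first value available comes one visit after randomisation.

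The Discussion itself expects reactions to allocation. It foresees that motivated women assigned to usual care may be disappointed and may withdraw or take up the exercise programme. Women in the intervention group may equally begin before the formal start. A first questionnaire at V0 can take up either reaction into the baseline.

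The endpoint is also self-reported, in a trial where only one arm is coached towards a weekly MET-hour target and keeps activity diaries. That makes differential reporting a plausible risk, and it is a reason to name an objective activity measure as well.

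The Discussion says that LIBRE-1 results will shape the programme of the larger trial. An activity change with an unclear starting point is weak input for that.

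**Working it through.** No sample size, power or alpha figure bears on this point. The check is a comparison of time points, followed by one identity.

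**1. First IPAQ, place by place**

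| Place in the protocol article | First IPAQ |
|---|---|
| Table 1 | V0 |
| Intervention group | V0 |
| Control group | V0 |
| International Physical Activity Questionnaire | SE |
| Study endpoints (baseline required) | SE |

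Three places start at V0, one starts at SE, and one needs an SE value. They cannot all be followed.

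**2. Is V0 in Table 1 just a misplaced mark?** The other measurements with a baseline (spiroergometry, accelerometry, nutrition questionnaires, laboratory, clinical examination, anthropometry, psychological questionnaires) all carry their first mark at SE. IPAQ alone starts at V0. That could suggest a slip in the table, but both group descriptions repeat V0, and each sets it against an SE start for the accelerometer in the same sentence. The text therefore does not settle which start is intended.

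**3. Count of year-1 time points in Table 1**
- IPAQ: V0, 3, 6, 9, 12 months = 5, none at SE.
- Accelerometry: SE, 3, 6, 9, 12 months = 5, which matches the five stated under Accelerometer.

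**4. What a V0 baseline does.** Let A be activity at SE, V0 and a later month t. Then

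A(t) − A(V0) = [A(t) − A(SE)] − [A(V0) − A(SE)].

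Any shift between SE and V0 is subtracted in full from the reported change. A rise before V0 makes the change look smaller, a fall makes it look larger, and no shift leaves it unaffected.

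**5. How much of the recall window follows allocation.** Let d be the number of days from allocation at SE to V0. The article does not give d, so it is treated as an assumption over its whole range. The part of the 7-day window after allocation is min(d, 7)/7: for d = 0 it is 0/7 = 0%, and for d of 7 or more it is 7/7 = 100%. Even at d = 0 the answers may be given by women who already know their arm. The documents do not narrow this range and give no activity shift to put into step 4, so no bias can be calculated.

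**6. Does the accelerometer have a pre-allocation baseline?** Randomisation and the first accelerometry share the SE column, and their order within SE is not stated. A device handed out at SE might record days after allocation. The accelerometer has an SE measurement, but the article does not show that it precedes the envelope.

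**The case against.** Several points on the other side are fair.

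- **A reader might infer that the IPAQ baseline is definitely post-randomisation.** The article does not support this as settled, because the IPAQ paragraph and Study endpoints both point to SE. What stands is the contradiction, together with what follows if sites work from Table 1.
- **SE in Study endpoints might loosely mean the value before the programme starts.** That reading would remove the contradiction in that section, but not the one with the IPAQ paragraph, and it would make the post-allocation value the baseline.
- **A reader might infer that accelerometry should replace IPAQ as the sounder measure.** This goes too far. Its own SE recording is not shown to precede allocation, IPAQ covers five areas of activity, and PAL is an average level rather than the MET-hour scale of the programme's target. It supports naming both, not demoting IPAQ.
- **The self-report risk is partly handled already.** The endpoint list is introduced as what the endpoints include, so it may not be exhaustive. VO2 max is listed and objective, and the Discussion uses accelerometry to monitor cross-over. This stands in part. VO2 max measures fitness rather than activity, and Table 1 schedules spiroergometry at SE, 3 and 12 months but not at 6. An activity measure left off the list is not clearly a prespecified endpoint.
- **A reader might infer that adjusting for a V0 baseline removes part of the treatment effect.** The article plans descriptive summaries by arm and tests against baseline. It states no covariate adjustment, so this harm cannot be claimed.
- **An article condenses the full protocol.** True, but the problem is not an omission. The article makes statements that conflict.

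**Conclusion.** The point holds as an inconsistency with a practical consequence. The physical-activity endpoint requires an SE baseline that the schedule does not collect, and the only alternative on that schedule is a 7-day self-report at V0, after randomisation at SE in an open trial. Such a baseline can reflect behaviour after women know their arm; it is not shown that it will.

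No size or sign can be attached. The SE-to-V0 interval is not given, and early starting, reduced activity and differential reporting could act in different directions. Any percentage would be invented.

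The reach is limited. IPAQ is one of several secondary endpoints, mainly descriptive, in a feasibility trial of at least 60 women sized on practical grounds. The primary endpoint in Table 4 rests on attendance, the 1-year visit, consent and exclusion criteria, and is unaffected. The correction is still worth making before recruitment: a questionnaire that looks back 7 days cannot recover a missing study-entry value later.

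The conclusion assumes that the SE column in Table 1 is the moment of allocation, as the table states, and that the blank IPAQ cell at SE is genuine, which both group descriptions support.

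**What to change.** 1. In Table 1, Intervention group and Control group, add IPAQ at SE for both arms, completed before the envelope is opened. This agrees with the IPAQ paragraph and with Study endpoints. A V0 questionnaire may stay, but not as the baseline.
2. In Study endpoints and in Statistical analysis and randomization, state that the IPAQ baseline is the pre-allocation SE value.
3. In Study endpoints, name accelerometer PAL as an objective physical-activity endpoint alongside IPAQ, and require its SE recording to be finished before allocation.
4. State the order of steps within SE: measurements first, then the envelope.

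**Cost.** No new visit, device or follow-up time point is needed. There is one more questionnaire at a first visit that the Discussion already describes as demanding, with examinations of about half a day. The envelope must also be held until the SE measurements, including the accelerometer recording, are complete, which may delay allocation for some women.
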